### Data collection methods

Data collection of participant-reported outcome measures will be carried out using online case report forms, or paper case report forms if participants prefer this. Participants will receive automated reminders by email and text/short message service (SMS). If they do not respond to this, then they will receive a telephone reminder at key time points, such as the 16-week questionnaire. Participants will also be sent a £10 gift voucher when the 16-week questionnaire is due and will be entered into a prize draw when they have completed the 52-week questionnaire.

Data collection from notes review will be carried out by practice staff using standardised questionnaires.

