### Interventions

Eligible children will be randomised 1:1 to either bath emollients plus standard eczema care or standard eczema care only. Standard eczema care in this study constitutes usual general practitioner (GP) care, supplemented by evidence-based guidance. We will provide basic information on eczema care at baseline to participants and GPs in the form of a booklet based on the National Institute for Health and Care Excellence (NICE) guidance^7^ (available on study website). Standard care includes advice to regularly use leave-on emollients plus intermittent topical corticosteroids if required. Standard care of eczema in the UK is generally delivered through 10 min consultations in primary care initiated by carers. GPs in the study will continue to refer to dermatology services when they feel this to be necessary. In the UK, referral criteria include: diagnostic uncertainty; eczema not satisfactorily controlled; child or carer may benefit from specialist advice on treatment application.^7^

Baseline appointments will be carried out by a trial coordinator at the participant's GP surgery (or at their home if surgery premises not available) and informed consent/assent will be sought at this point. At the baseline appointment, both groups will be given basic information about eczema and will be given identical verbal and written information on how to wash children with eczema as soap avoidance is an important component of eczema care. This information is also available on the study website. We will ask all carers to either wash their child with water alone or to use a leave-on emollient as a soap substitute. If they have difficulties with this and request to use an emollient wash product then they may do so. Guidelines on frequency of bathing vary, but most healthcare professionals advise daily bathing for children with eczema^23^ and this advice is offered in our information to carers.

Children allocated to receive bath emollients will receive a prescription for a bath emollient from a GP in the participating practice and we will ask the prescriber to enter this as a ‘repeat’ prescription, so that carers may obtain further supplies as necessary, reflecting usual prescribing in UK primary care. Carers will be asked to use bath emollients as prescribed or described on the packaging, to reflect how they are used in usual practice.

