The British National Formulary (BNF) lists 13 different bath emollients, but in clinical practice, a few of these are commonly prescribed. We will encourage participating practices to prescribe one of the following products: Oilatum Fragrance Free Junior, Balneum bath oil or Aveeno Bath Oil. These products account for the majority of bath emollient prescriptions issued in the UK^8^ and appear in local prescribing formularies for participating centres. Participants may express a preference for one brand of bath emollient over another, or if no preference is expressed, the choice of prescription will be determined by the GP. If children or carers wish to change bath emollient during the trial then they may change to an alternative within the three above, or choose a different bath emollient if their GP is happy to prescribe this. Prescribers will be asked to avoid bath emollients that contain additional ingredients such as antipruritics and antiseptics.

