▸ Consultation record mentions flare of eczema or infected eczema or prescription or advice to use topical corticosteroids/calcineurin inhibitors or antibiotics (topical or oral antibiotics for skin).

▸ Consultation record mentions eczema but with no indication that this was an eczema flare or infected eczema.

▸ Consultation record mentions skin rash, itch or dryness mentioned but no mention of eczema.

▸ Consultation recorded with no mention of eczema or skin rash, itch or dryness.

CHU-9D, Child Health Utility 9D; DFI, Dermatitis Family Impact; GP, general practitioner; NESS, Nottingham Eczema Severity Scale; POEM, Patient-Oriented Eczema Measure.

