#### Secondary outcome measures

Secondary outcomes include differences between groups in POEM scores captured monthly over 12 months.

We will analyse differences between groups in number of eczema exacerbations resulting in a primary healthcare consultation over 12 months measured by GP notes review. Exacerbations will be defined as consultations where there is mention of eczema and topical steroid or topical calcineurin inhibitor has been advised or prescribed (see table 1 schedule of observations for further detail). We will also measure dermatology referrals and prescribing for eczema over 12 months by GP notes review. We will assess service use and medication use by carer report, in addition to GP notes review.

We will ask both groups about use of bath emollient in order to assess adherence to treatment allocation. Adverse effects of bathing, such as stinging in the bath or slipping in the bath or bathroom will also be asked in both groups to allow exploration of any differences between groups.

Differences between groups in change from baseline in disease-specific quality of life at 4 and 12 months will be measured by Dermatitis Family Impact (DFI). DFI^26^ is a widely used validated instrument measuring impact of eczema on the family's quality of life.

We will measure differences between groups in change from baseline in generic quality of life at 4 and 12 months, using the Child Health Utility 9D (CHU-9D).^27^ The use of EQ-5D in children has been questioned and it does not capture quality of life issues pertinent to childhood eczema. The CHU-9D is a paediatric generic preference-based utility measure exclusively developed with children aged 7–11 years and is more suitable for capturing quality of life impact related to eczema, such as sleep disturbance and child's mood. Personal communication with the team who developed this measure confirmed that studies are underway trialling its application in children aged 5–7 years but, to our knowledge, there are no studies reporting for infants. There are no suitable utility measures validated for very young children aged 1–4 years, but the CHU-9D performed well in a similar population in the SPaCE feasibility trial (CHU-9D data currently being prepared for publication).^28^

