## Methods

### Assignment of interventions

Participants will be randomly allocated to treatment group using computer-generated random sequence, stratifying by region. Bath emollients make the bath feel ‘greasy’, and it is therefore not possible to make a convincing placebo, particularly as a survey carried out prior to the study suggested that many families of children with eczema have experience of using bath emollient (see table 2). As discussed above, the main focus for this pragmatic study is patient-centred, and primary outcome is therefore a participant/proxy-reported score. Care providers and clinical studies officers will not be blinded as they are involved in ensuring participants receive the correct treatment and may be involved in discussing adherence with participants over the course of the year. Furthermore, the additional staff cost that would have been incurred by having researchers ‘blind’ to group allocation did not seem justifiable if the primary outcome is participant-reported. The trial statistician will remain blinded to treatment allocation.

**Table 2 BMJOPEN2015009575TB2:** Pretrial survey findings

How many times a week does your child have a bath? (n=211)		
Less than once a week	19	(9%)
1–2 times per week	47	(22.3%)
3–4 times per week	57	(27%)
5–6 times per week	25	(11.8%)
7 times per week	55	(26.1%)
More than 7 times per week	4	(1.9%)
How many times a week does your child have a shower? (n=211)		
Less than once a week	127	(60.2%)
1–2 times per week	39	(18.5%)
3–4 times per week	19	(9%)
5–6 times per week	5	(2.4%)
7 times per week	7	(3.3%)
More than 7 times per week	2	(0.9%)
What do you use to wash your child's face, hands and body? (n=209)		
Emollient moisturiser	62	29.7%
Bath emollient	128	61.2%
Soap substitute	19	9.1%
Normal soap or body wash	21	10%
Water only	40	19.1%
Other	22	10.5%
What do you use to wash your child's hair? (n=209)		
Emollient moisturiser	7	3.3%
Bath emollient	23	11%
Normal shampoo	44	21.1%
‘Sensitive’ or fragrance free shampoo	101	48.3%
Water only	18	8.6%
Other	41	19.6%
Do you put bath emollients in your child's bath? (n=207)		
Yes, all the time	117	56.5
Yes, almost all the time	30	14.5
Yes, more than half the time	10	4.8
Less than half the time	14	6.8
Rarely	9	4.3
Never	27	13%
Do you think bath emollients help your child's eczema? (n=150)		
Yes	69	46%
No	12	8%
Unsure	69	46%

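### The exacerbation count from GP notes is collected by staff who can normally see the allocation, the cost reason for not using blinded researchers does not cover it, and the event is defined in two different ways

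*Protocol article*

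**What the plan says.** All references are to the protocol article.

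- **Outcome.** Secondary outcome measures lists the "number of eczema exacerbations resulting in a primary healthcare consultation over 12 months measured by GP notes review". It then gives a rule: "Exacerbations will be defined as consultations where there is mention of eczema and topical steroid or topical calcineurin inhibitor has been advised or prescribed". For further detail it points to Table 1.
- **Consultation groups.** The footnote to Table 1 sorts consultations into four groups. The first is "Consultation record mentions flare of eczema or infected eczema or prescription or advice to use topical corticosteroids/calcineurin inhibitors or antibiotics", where the antibiotics may be topical or oral, for skin. The second is "Consultation record mentions eczema but with no indication that this was an eczema flare or infected eczema".
- **Who collects.** Under Data collection methods: "Data collection from notes review will be carried out by practice staff using standardised questionnaires".
- **What the practice knows.** Under Interventions, a child allocated to bath emollient "will receive a prescription for a bath emollient from a GP in the participating practice", and the prescriber is asked to enter it as a repeat item. Under Intervention adherence, practices are advised on maintaining allocation. Table 1 shows that the same notes review also collects medication use.
- **Blinding.** Assignment of interventions leaves care providers and clinical studies officers unblinded because they help to deliver the allocated treatment. It adds that the cost of blinded researchers "did not seem justifiable if the primary outcome is participant-reported". The trial statistician is the only person said to be blinded.
- **Use.** The Health economic analysis has two cost-effectiveness units. One is cost per exacerbation avoided over a year, with POEM at one year as the fallback.

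**The concern.** In an open trial, a count read from free-text records by someone who knows the arm can be shifted by expectation when an entry is unclear. The plan argues for doing without blinded researchers, but the argument concerns an outcome that no researcher assesses. The exacerbation count is a different kind of outcome: someone at the practice reads a record and decides what it contains. The Discussion treats bias only for the participant-reported measure, so this route is neither controlled nor acknowledged.

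Two non-identical definitions of the event make this worse. Where they disagree, someone must choose, and nothing stated prevents that choice from being made by a person who can see the allocation.

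At stake are one secondary clinical comparison and one of the two cost-effectiveness ratios.

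**Working it through.** No figure in the protocol is in dispute, so the check is mainly a comparison of sections.

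**1. Can the extractor see the arm?** In the intervention arm, normally yes. The product is a repeat item issued by the same practice, and medication use is part of the same review. This is an inference, though a strong one. It is weaker for controls. In the pretrial survey (Table 2), 117 of 207 carers (56.5%) said that they always put bath emollient in the bath, so control records may also hold earlier bath emollient items.

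**2. Does the stated rationale reach this outcome?** Two reasons are given. Delivery of treatment explains why practice staff know the allocation; it says nothing about outcome assessment. The cost of blinded researchers does bear on outcome assessment, but it is conditional on the primary outcome being participant-reported. Neither covers a record-based secondary outcome.

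**3. Do the two definitions agree?** Applying each as written:

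| Record content | Secondary outcome text | First group, Table 1 footnote |
|---|---|---|
| Eczema mentioned, topical steroid or calcineurin inhibitor prescribed or advised | Exacerbation | Yes |
| Eczema flare noted, neither treatment prescribed or advised | Not an exacerbation | Yes |
| Infected eczema, antibiotic only | Not an exacerbation | Yes |
| Eczema mentioned, antibiotic for skin only, no flare or infection noted | Not an exacerbation | Yes |

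The definitions agree on the first row and differ on the other three. In addition, a consultation that mentions eczema and renews a steroid, with no sign of a flare, meets the first group through the prescription and also fits the literal wording of the second.

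**4. Where does judgement enter?** A prescription is a recorded fact. Whether treatment was *advised*, and whether the text *mentions* a flare, must be read from the notes.

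**5. How much could it matter?** The protocol gives no exacerbation rate and no share of unclear records. Both calculations below are illustrations on assumed inputs with no true effect.

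*Shift in the rate ratio.* Suppose that a share b of candidate consultations is borderline, and that 60% of these are coded as events in controls against 40% in the intervention arm.
- b = 0.30: control 0.70 + 0.30 × 0.60 = 0.88; intervention 0.70 + 0.30 × 0.40 = 0.82; ratio 0.82/0.88 = 0.93.
- b = 0.50: control 0.50 + 0.50 × 0.60 = 0.80; intervention 0.50 + 0.50 × 0.40 = 0.70; ratio 0.70/0.80 = 0.875, or about 0.88.

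*False-positive rate.* Take n = 338/2 = 169 per arm (Sample size section), λ = 1 or 2 events per child-year, overdispersion k = 0 or 1, and a fraction d of events not credited in one arm. Then

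SE = √{[(1/λ + k) + (1/(λ(1 − d)) + k)]/n}, t = |ln(1 − d)|/SE, and the rejection rate is 1 − Φ(1.96 − t) + Φ(−1.96 − t).

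Worked case with λ = 1, k = 0, d = 0.10: SE = √[(1 + 1.111)/169] = 0.112; t = 0.105/0.112 = 0.94; rejection rate 0.156.

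| d | Lowest (λ = 1, k = 1) | Highest (λ = 2, k = 0) |
|---|---|---|
| 5% | 6.3% | 10.1% |
| 10% | 10.4% | 26.6% |
| 20% | 29.1% | 78.1% |

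The nominal rate is 5%.

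**The case against.** The strongest reply is that the text does not say who assigns the four groups. Practice staff collect the data; the footnote uses the passive. The extraction form is not shown, and it may already ask only for facts. That stands: coding by practice staff is the natural reading, not a stated one.

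Second, the rule in the outcome text asks only for a mention of eczema and a treatment prescribed or advised. No verdict on flare is needed, and much of the rule is factual. This also stands. It narrows the scope for judgement without closing it, and it does not remove the conflict with Table 1.

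Third, carers start consultations and know the allocation, so the count can be affected before anyone reads a record. This is true, and no coding rule cures it.

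Three stronger readings are tempting and are not supported:

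- *Only the intervention arm has GP contacts driven by the protocol, which inflates its count.* The Interventions section requires a prescription, not a consultation. A carer may change product, or "choose a different bath emollient if their GP is happy to prescribe this", but that is the carer's wish. Carers in both arms are told to see the GP if eczema worsens.
- *The count is biased by a known amount or in a known direction.* The borderline shares, the 60% against 40% split and the values of d are assumptions with no anchor in the document.
- *No reason at all is given for unblinded practice staff.* One is given, about delivering treatment. What is missing is a reason that bears on assessing this outcome.

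**Conclusion.** The point holds in a limited form. Notes-review data for a secondary outcome are collected by staff who can normally see the allocation, at least in the intervention arm. The cost reason for not using blinded researchers covers only the participant-reported primary outcome, and the event has two differing definitions. The definitional conflict rests on the text alone. Visibility of the arm is an inference from the repeat prescription and the advice to practices.

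The size of any bias is unknown. The rate ratios of 0.93 to 0.88 and the false-positive rates show only that modest differential coding would be enough to matter. The primary POEM result is untouched. The cost per exacerbation avoided is exposed, but it is one of two units and has a POEM fallback. The point is worth correcting because the correction is cheap.

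**What to change.** 1. Reconcile the outcome text and the Table 1 footnote into one definition of an exacerbation, with consultation groups that cannot overlap.
2. Have practice staff record only facts for each consultation: date; eczema mentioned or not; words for flare or infection present or not; each topical steroid, calcineurin inhibitor or antibiotic prescribed or advised.
3. Derive the consultation group and the exacerbation count centrally, with a fixed program run without allocation. Hold bath emollient prescribing, which the costing still needs, in a separate file.
4. State as a limitation that practice staff still extract the facts unblinded, and that unblinded carers and GPs can influence whether a consultation or prescription happens at all.

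Contacts made only to issue or change a bath emollient should stay in the main count. Excluding them would remove events mainly from one arm; at most it is a sensitivity analysis.

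The cost is a revised form with a few more fields per consultation and a short derivation program. No extra reader is needed.

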### Data management

Participants will enter their outcome data online into a validated database. Data will be stored on a secure server at the University of Southampton. Data collection from notes review and from participants who prefer to complete paper-based will be stored on paper in secure filing cabinets.

### Statistical methods

We will use repeated measures ANCOVA to explore whether there is a significant difference between mean POEM scores over the 16-week period in the intervention and standard care groups. The analysis will control for possible confounding effects of key covariates, such as baseline eczema severity and age of child. However, because ANCOVA relies on analysis of complete cases only, the levels of missing data will be reviewed and, if appropriate, the data will be analysed using mixed models instead, which allows incomplete cases to contribute to the analysis. There will be no interim analyses.

For the analysis of secondary outcomes, repeated measures analysis in line with that used for the primary outcome will be used for the monthly POEM measure up to 1 year. For other secondary outcomes, linear regression will be used for continuous outcomes if the assumptions are met. Otherwise non-parametric analyses will be used. Logistic regression will be used for dichotomous outcomes and a suitable count model, as determined by goodness of fit measures, for count data. All analyses will control for potential confounders.

Primary analyses will be carried out on an intention to treat basis, according to the CONSORT definition^31^ whereby all participants are included in the group to which they were assigned, whether or not they completed the intervention given to the group. We will consider carrying out a per protocol analysis in addition to this if monitoring reveals a substantial proportion are not following their treatment allocation (ie, intervention group stop using bath emollient or control group start bath emollient). We will carry out a sensitivity analysis based on prior belief in bath emollients, to explore whether this appears to have any influence on outcomes. The statistical methods will be finalised in a statistical analysis plan, which will be made available on the study website.

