**Methods and analysis:**

*Design*: Pragmatic open 2-armed parallel group randomised controlled trial. *Setting*: General practitioner (GP) practices in England and Wales. *Participants*: Children aged over 12 months and less than 12 years with eczema, excluding inactive or very mild eczema (5 or less on Nottingham Eczema Severity Scale). *Interventions*: Children will be randomised to either bath emollients plus standard eczema care or standard eczema care only. *Outcome measures*: Primary outcome is long-term eczema severity, measured by the Patient-Oriented Eczema Measure (POEM) repeated weekly for 16 weeks. Secondary outcomes include: number of eczema exacerbations resulting in healthcare consultations over 1 year; eczema severity over 1 year; disease-specific and generic quality of life; medication use and healthcare resource use; cost-effectiveness. Aiming to detect a mean difference between groups of 2.0 (SD 7.0) in weekly POEM scores over 16 weeks (significance 0.05, power 0.9), allowing for 20% loss to follow-up, gives a total sample size of 423 children. We will use repeated measures analysis of covariance, or a mixed model, to analyse weekly POEM scores. We will control for possible confounders, including baseline eczema severity and child's age. Cost-effectiveness analysis will be carried out from a National Health Service (NHS) perspective.

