### Outcomes

#### Primary outcome measure

Our primary outcome measure is difference between the two treatment groups in long-term control as measured by POEM scores captured weekly over the first 16 weeks. POEM is a patient-reported outcome based on symptoms over the previous week which can be completed by the child's carer or the child themselves.^24^ POEM is the only patient-reported outcome that demonstrated sufficient validity and repeatability in a systematic review of outcome measures for eczema^25^ and has been recommended as the preferred instrument for capturing patient-reported symptoms in eczema trials by the Harmonizing Outcome Measures for Eczema initiative (http://www.homeforeczema.org). Our primary outcome measure is based on repeated measures of POEM data collected weekly over 16 weeks because this reflects the impact of this relapsing and remitting chronic condition better than comparing outcomes at a single follow-up point. However, if weekly questionnaires prove too burdensome for participants and there is excessive missing data, we will consider change in POEM score from baseline to 4 months as our primary outcome.

Because of the burden of weekly questionnaires on participants, we have limited weekly data collection to the first 16 weeks of the trial for the primary outcome assessment but follow-up will continue for 12 months. Participants may choose to complete questionnaires either online or by post. See table 1 for schedule of observations.

**Table 1 BMJOPEN2015009575TB1:** Schedule of observations

Outcomes collected	Prescreen	Baseline	Weekly for 15 weeks	16 weeks	4 weekly for 32 weeks	52 weeks
Carer-reported outcomes						
UK diagnostic criteria for eczema	✓	✓				
Eczema severity over past year (NESS)	✓					
Demographics		✓				
Prior belief in bath emollients	✓	✓		✓		✓
Service use		✓		✓	✓	✓
Medication use		✓		✓	✓	✓
Eczema severity over past week (POEM)		✓	✓	✓	✓	✓
Eczema-related quality of life (DFI)		✓		✓		✓
Generic quality of life (CHU-9D)		✓		✓		✓
Questions about washing		✓		✓		✓
Adverse effects from bathing		✓	✓	✓	✓	✓
Adherence/avoidance of bath emollients	✓	✓		✓		✓
Review of GP records for 12 months from recruitment						
Number of consultations*						✓
Referrals for eczema						✓
Medication use						✓

*Consultations will be categorised into the following four groups:

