### Sample size

The sample size was calculated for repeated measures analysis of covariance (ANCOVA) in weekly POEM scores over 16 weeks. Using data from a similar population in the SWET trial,^30^ we aim to detect a mean difference of 2.0 (SD 7.0) between intervention and control groups. An α of 0.05 and power 0.9 gives a sample size of 338. Allowing for 20% loss to follow-up, this gives a total sample size of 423 children.

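### A complete-case repeated measures ANCOVA is the default for 16 weekly POEM scores; the mixed model, now only a fallback, should be the primary analysis from the outset

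*Protocol article*

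**What the plan says.** The Statistical methods section of the protocol article opens with the default: "We will use repeated measures ANCOVA to explore whether there is a significant difference between mean POEM scores over the 16-week period". It then acknowledges the limitation and makes any change of method conditional: "because ANCOVA relies on analysis of complete cases only, the levels of missing data will be reviewed and, if appropriate". The fallback that completes this sentence reads: "the data will be analysed using mixed models instead, which allows incomplete cases to contribute to the analysis". The abstract lists the two methods without ranking them: "We will use repeated measures analysis of covariance, or a mixed model, to analyse weekly POEM scores".

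Three other places show that missing weekly scores are expected:

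- Primary outcome measure: if the weekly forms prove too great a burden and "there is excessive missing data, we will consider change in POEM score from baseline to 4 months as our primary outcome".
- Sample size: "Allowing for 20% loss to follow-up, this gives a total sample size of 423 children".
- Data collection methods: automated reminders go out by email and text, but telephone reminders are kept for key time points, of which the 16-week form is the example. The voucher is also tied to week 16.

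Statistical methods also sets an intention-to-treat rule ("all participants are included in the group to which they were assigned, whether or not they completed the intervention given to the group") and defers the final detail: "The statistical methods will be finalised in a statistical analysis plan, which will be made available on the study website".

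**The concern.** The primary outcome is a series of 16 weekly scores per child. By the article's own account, the method named first uses only children with the full series, so one missed form in 16 removes a randomised child and all the scores that the child did provide. The design foresees such gaps, and its most active chasing is reserved for key time points.

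Two things are at stake. The first is precision: the target of 338 analysable children would have to be met by children with no missing score at all. The second is bias: families who return every form are a selected group. In an open trial with a carer-reported outcome, full completion may depend on allocation or on how the eczema is doing. The mixed model already in the plan avoids discarding these children, so there is little reason to hold it back as a second choice.

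**Working it through.** **Inputs from the protocol article.** Difference 2.0, SD 7.0, α 0.05 (two-sided assumed), power 0.9, 338 children before loss, 20% loss and 423 in total (Sample size); 1:1 allocation (Background); 16 scores per child, being 15 weekly forms plus the 16-week form (Table 1). No weekly return rate and no correlation between scores is given.

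**The plan's own figures.** 338/(1 − 0.20) = 422.5, rounded up to 423, which reproduces. A plain two-group comparison needs 2 × [7.0 × (1.960 + 1.282)/2.0]² ≈ 257.4, so 258 per arm and 516 in total, not 338. With the mean of 16 scores the variance factor is (1 + 15ρ)/16. Setting it to 338/514.9 = 0.656 gives ρ ≈ 0.63. Since ρ is not stated, 338 can be neither confirmed nor called wrong. I take 90% power at 338 as given.

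**Power with n complete children.** This calibration implies an effective SD of 7.0 × √0.656 ≈ 5.67, so power ≈ Φ(2.0/(5.67 × √(4/n)) − 1.96), or equivalently Φ(3.24 × √(n/338) − 1.96).

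**Independent misses (assumed rates).** Complete children = 423 × (1 − q)¹⁶, where q is the share missed per weekly form.

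| q | share complete | complete of 423 | power |
|---|---|---|---|
| 1% | 0.851 | 360 | 0.917 |
| 2% | 0.724 | 306 | 0.870 |
| 3% | 0.614 | 260 | 0.811 |
| 5% | 0.440 | 186 | 0.672 |
| 10% | 0.185 | 78 | 0.345 |

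Keeping 338 complete children requires q ≤ 1 − (338/423)^(1/16) ≈ 1.4%.

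**Clustered misses (assumed rates).** Misses usually concentrate in some families. A beta-binomial model with mean missing share μ and within-child correlation ICC has a = (1 − μ)(1 − ICC)/ICC and b = μ(1 − ICC)/ICC. The share complete is B(a + 16, b)/B(a, b).

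| μ | ICC | complete of 423 | power, complete cases | children with at least one score |
|---|---|---|---|---|
| 5% | 0.1 | 261 | 0.812 | 423 |
| 5% | 0.5 | 356 | 0.915 | 421 |
| 5% | 0.9 | 395 | 0.939 | 408 |
| 10% | 0.1 | 158 | 0.601 | 423 |
| 10% | 0.5 | 299 | 0.862 | 419 |
| 10% | 0.9 | 368 | 0.922 | 392 |
| 20% | 0.1 | 55 | 0.257 | 423 |
| 20% | 0.5 | 208 | 0.719 | 413 |
| 20% | 0.9 | 315 | 0.879 | 359 |

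The last column counts the children whom a mixed model could use: 359 to 423 in these cases. The complete-case count ranges from 55 to 395.

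**The case against.** The strongest reply is that the authors saw the problem and wrote the remedy into the same sentence. The worst figures above arise only if complete-case ANCOVA is kept with most children incomplete, which is where a review of missing data would most plausibly lead to the mixed model. At 2% missed per week, where ANCOVA might well be retained, power is still 0.870. The stated trigger is the level of missing data, not POEM results by arm; the trial statistician is blinded to allocation; and no interim analysis is planned. This does not look like picking a model by its result. A threshold for the switch is ordinary content for the statistical analysis plan, which is not shown. All of this stands. The point therefore rests on the order of the two methods, which the article does state, and not on the absent threshold.

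Two stronger readings are tempting, and the text supports neither.

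- A reader might infer that complete-case analysis contradicts the intention-to-treat rule. That sentence concerns whether children completed the intervention and stay in their assigned group; the next one contrasts it with a per protocol analysis of those not following allocation. It does not address missing outcome forms. Dropping children for a missed form sits uneasily with it, but is not a contradiction.
- A reader might infer a conflict with the 20% allowance. The article does not define loss to follow-up as either complete dropout or any missed form. The allowance would cover a complete-case analysis if no more than about 20% of children missed any form, and the text does not exclude that reading.

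**Conclusion.** The concern holds in a limited form. The article makes a method that it calls complete-case the default for a 16-score outcome in which it expects gaps, and treats the better method as conditional. If the default were kept, modest scattered missingness would be costly: 5% missed per week would leave about 186 of 423 children and power near 0.67. If misses were strongly clustered the loss would be small: at 10% missing on average with ICC 0.9, 368 children would remain, above the 338 target.

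These figures rest on assumed return rates, on taking the stated 90% power at 338 as correct, and on the same variance among completers as among all children. The direction of any selection bias cannot be judged from the document. Because the mixed model is already written in as a fallback, this is an improvement worth making before analysis and not a defect that undermines the trial.

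**What to change.** In Statistical methods, and in the matching sentence of the abstract, name the linear mixed model for repeated measures as the primary analysis from the outset. It should use all available weekly POEM scores and adjust for baseline POEM, age and region, region being the randomisation stratum. Remove the conditional switch, and keep complete-case ANCOVA, if wanted, as a sensitivity analysis only.

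The cost is one paragraph, carried through to the statistical analysis plan, with no extra data or participants. The downside is negligible: when few scores are missing, the two analyses use nearly the same children. The mixed model still assumes that missingness is explained by the observed scores and covariates, so it reduces the exposure to selection bias without removing it.
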